## 1 Introduction

Selective screening is an essential tool for diagnosing various types of inborn errors of metabolism (IEM). IEMs are a group of phenotypically and genotypically heterogeneous metabolic disorders caused by mutations in genes encoding enzymes of metabolic pathways or receptors. Deficiency or change in the activity of necessary enzymes or other proteins in intermediate metabolic pathways leads to the accumulation or deficiency of the corresponding metabolites in cells or body fluids, manifesting in a wide range of diseases with clinical heterogeneity, thus complicating their diagnosis (Mak et al., 2013). The classification of existing IEM is based on the biochemical properties of the substances involved (Han et al., 2015). Although these disorders are rare individually, they are numerous in the aggregate (Ozben, 2013). Many IEM do not have specific clinical signs and are difficult to diagnose using only clinical manifestations or routine laboratory tests (Champion, 2010). Most often, IEMs occur in early infancy and childhood, and the prevalence within different racial and ethnic groups is not the same. Hence, there are population differences in the incidence of IEM (Champion, 2010; Lampret et al., 2015; Shibata et al., 2018; Sarker et al., 2019). IEMs typically lead to irreversible neurological and psychological damage and/or disability or death in affected children. Early diagnosis of IEM can significantly reduce the risk of death and may prevent long-term neurological complications (Lampret et al., 2015; Dietzen et al., 2016). The purpose of NBS (newborn screening) is to presymptomatically identify infants with congenital conditions so that treatment can be started as early as possible and prevent or mitigate the long-term consequences of the condition. The expanded newborn screening program increased the screening panel of disorders from six (6) to more than twenty-eight (Pitt, 2010). IEMs represent the largest category of hereditary diseases amenable to causal therapy (van Karnebeek and Stockler-Ipsiroglu, 2014).

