#### 2.2.4 Criteria for inclusion in the selective screening for IEM

Children from 1 day to 18 years of age will be enrolled for selective screening for IEM if one of the main criteria or two or more additional criteria (symptoms) are identified. The inclusion criteria for IEM selective screening are presented in Table 2.

**TABLE 2 T2:** Criteria for inclusion in the selective screening for IEM.

Main criteria (symptoms)	Sudden deterioration in the clinical condition of the child after a period of normal development (days, weeks, months): Acute metabolic encephalopathy lethargy (coma) seizures resistant to antiepileptic therapy
	Hepatomegaly (hepatosplenomegaly)
	Metabolic acidosis with increased anion gap
	Multiple fractures
	Child mortality in the family from diseases with similar symptoms
Additional criteria (symptoms)	Treatment-resistant seizures
	Abnormal muscle tone: dystonia, hyperkinesis, hypotension
	Speech retardation
	Mental retardation of unknown cause
	Cardiomyopathy
	Tachypnea
	Frequent spitting up (vomiting)
	Osteoarticular anomalies (joint stiffness, chest deformity, rickets-like changes)
	Hernias (umbilical, inguinal-scrotal)
	Persistent or recurrent hypoglycemia
	Metabolic alkalosis
	An increase in ketone bodies in the blood and (or) urine
	Hyperammonemia
	An increase in the level of liver enzymes (ALAT, AST) more than 1.5 times
	Increase in the level of creatine phosphokinase (CPK) by more than 2 times
	Decrease in the level of alkaline phosphatase (AP) below the age norm
	Imaging or electrophysiological examinations indicating a metabolic disorder
	Leukopenia
	Thrombocytopenia
	Abnormal odor of urine, body, earwax, any unusual odor
	Hair growth disorders, alopecia
	Ophthalmic anomalies
	Unusual appearance, dysmorphic features
	History of death of a previous sibling of unknown cause
	Parents’ consanguinity
	Positive family history with metabolic disorders

Exclusion criiteria:

Patients having the following conditions will be excluded:1. Perinatal brain injury,2. Brain injury,3. Infections of the central nervous system,4. Toxicological diseases,5. Tumors,6. Chromosomal abnormalities,7. Symptoms specified in the Inclusion criteria, but with a confirmed diagnosis of any disease other than Amino acid disorders (AAD), Fatty acid oxydation disorders (FAOD), or Organic acidemias (OA).

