### 3.4 Presenting IEM frequencies in the child population

The frequency of inborn errors of metabolism detected using tandem mass spectrometry, depending on the geographical location and type of IEM in western Kazakhstan during the period from 2023 to 2024, can be represented graphically in the form of accumulation diagrams demonstrating the contribution of AAD, OA, and FAOD to the total incidence of IEM. Also, these data can be presented in the form of a table. The data will include the total number of IEM cases in the high-risk group of children and the absolute number and frequency of cases for each identified disease. Detection rates for selective screening and incidence will be calculated according to the number of children born in western Kazakhstan during the study period, in 2023–2024, for each specific disease. These data will allow for estimating the number of affected male and female children and determining which IEMs were the most common in the studied population. Given that selective screening of the child population in western Kazakhstan will be carried out for about 2 years (2023–2024, recruitment of high-risk children), the incidence rate for each class of disorders (AAD, OA, FAOD) will be established, taking into account the total number of births each year.

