## 4 Discussion

The present study assumes only selective screening for IEM. Implementing ENBS, which allows for thoroughly assessing the prevalence of IEM in the child population of western Kazakhstan, is currently unavailable due to a lack of proper financing. In addition, given that the overall prevalence of IEM in populations is relatively low, less than 1:100,000 for most of them, coverage for expanded newborn screening should be total. Besides, it is known that not all IEMs are diagnosed during ENBS, as some disorders debut at a later age (Hassan et al., 2016). Nonetheless, the data of selective screening conducted among children at high risk of IEM, given the inclusion in the study of the largest pediatric hospitals in western Kazakhstan, can serve as a basis for calculating the relative frequencies of various IEMs in the child population of the region.

Detection rates for selective screening and incidence will be calculated according to the number of children born alive in the region during the study period, in 2023–2024, for each specific disease. These data will allow for estimating the number of affected male and female children and determining which IEMs are the most common. The frequencies of each IEM revealed across the child population of western Kazakhstan will be matched with incidence data in other regions of the world.

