Conducting ENBS and selective screening for IEM in Kazakhstan is of particular interest due to the entire absence of similar studies in the region of Central Asia, despite a significant number of studies conducted in neighboring areas (Russia, China, India, the Middle East, countries of East and Southeast Asia) (Guthrie and Susi, 1963; Nagaraja et al., 2010; Shibata et al., 2018; Therrell and Padilla, 2018; Yang et al., 2020; Deng et al., 2021; Loeber et al., 2021). A study by Shibata et al. revealed different rates of IEM incidence and spectrum of diseases in Asian countries. In addition, it was found that the ranges of IEM diseases determined using selective screening differed from those detected using ENBS (Shibata et al., 2018). For instance, the incidence of phenylketonuria in Asians (∼1:50,000 in Korea; ∼1:110,000 in Japan) is much lower than in Caucasians (∼1:10,000). The medium-chain acyl-CoA dehydrogenase (MCAD) deficiency, a common genetic metabolic disorder in Caucasian children with the A985G mutation of frequent occurrence, can serve as another example. Unlike Caucasians, MCAD is extremely rare in Korea and Japan (Vieira Neto et al., 2012). The frequencies (specific contribution to the IEM spectrum) of FAOD in the United States newborn population are, according to various studies, 45.2% in North Carolina (Frazier et al., 2006) and 38% in California (Feuchtbaum et al., 2012), which is slightly higher than in some European countries (Lindner et al., 2011; Shibata et al., 2018) and much exceeds the frequency of FAOD in Asian countries (Guthrie and Susi, 1963; Golbahar et al., 2013; Selim et al., 2014; Hassan et al., 2016; Shibata et al., 2018). FAOD detection rates for selective screening vary across countries, ranging from 0.29% in a South Korean study (Yoon et al., 2005) to 10.8% in a study in Oman (Al Riyami et al., 2012).

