Thus, the number of IEMs to be included in the protocol of the future ENBS in Kazakhstan through LC-MS/MS will depend, in addition to economic factors and laboratory equipment, on the frequency of diseases established during selective screening. In describing established cases of IEM, in addition to presenting the data specified in the Results section, the present study implies reflecting the family history of IEM, including the number of patients and families with IEM, gender, positive family history, consanguineous marriages, and age of the symptoms onset. Although, due to the historically and socially established forbiddance for consanguineous marriages in Kazakhstan, we assume their rare prevalence, the data obtained would be of interest for comparison with populations for which similar results are already available (Guthrie and Susi, 1963; Al Riyami et al., 2012; Golbahar et al., 2013; Hassan et al., 2016; Gayduk et al., 2022).

In the present study, the distribution of IEM primary clinical symptoms and their severity will be analyzed by age. Delayed diagnosis at an older age is commonly associated with many severe and irreversible clinical complications in patients (Champion, 2010; Selim et al., 2014; Han et al., 2015; Lampret et al., 2015; Dietzen et al., 2016). This circumstance calls for the urgent need for early detection and intervention to achieve favorable outcomes in IEM.

• Study limitations.1. The number of children with clinical manifestations to be examined in the ongoing screening for IEM by LC-MS/MS is limited.2. Other parts of Kazakhstan are not involved in the study. As such, assessing the differences between the levels of AAs, ACs, and SuAc in DBS of the child population and the differences in the IEM incidence appear impossible.3. The need for multiple and expensive tests to rule out rare and ultra-rare IEM.4. Metabolites for diagnosing other hereditary metabolic diseases, such as disorders of carbohydrate metabolism, disorders of porphyrin metabolism, disorders of purine and pyrimidine metabolism, disorders of steroid metabolism, disorders of mitochondrial function, disorders of peroxisomal function, and lysosomal storage disorders, are not included in this study.

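### Per-disease frequencies from a referred, mostly symptomatic group are to be matched with incidence elsewhere and to inform the newborn panel, although the article itself reports that selective and newborn screening find different spectra

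*Protocol article*

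**What the plan says.** - **Design and entry.** The Discussion opens with "The present study assumes only selective screening for IEM". Under Section 2.2.4 a child enters "if one of the main criteria or two or more additional criteria (symptoms) are identified". Most criteria in Table 2 are symptoms or abnormal test results; a few concern family history.
- **Contrast with newborn screening.** The Introduction gives the purpose of newborn screening as "to presymptomatically identify infants with congenital conditions so that treatment can be started as early as possible".
- **Quantity computed.** Section 3.4 and the Discussion calculate incidence for each disease from the cases found and the live births in the region in 2023–2024. Section 3.4 expects this to allow "determining which IEMs were the most common in the studied population".
- **External comparison.** The Discussion says the frequency of each disorder "will be matched with incidence data in other regions of the world". Task 3 in the Introduction likewise plans comparison with published reports from other populations. Neither passage says which type of programme may serve as comparator.
- **Use.** The Discussion says that the number of disorders in the future ENBS protocol will depend, besides economics and laboratory equipment, "on the frequency of diseases established during selective screening".
- **The article's own caution.** Citing a review of Asian countries, the Discussion reports that "the ranges of IEM diseases determined using selective screening differed from those detected using ENBS". None of the four listed limitations takes this up.

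**The concern.** A newborn programme counts affected infants among all births, mostly before symptoms. This study counts affected children among those referred and sampled. Dividing the second count by all births does not turn it into the first. A disorder that is mild, clinically silent in childhood, fatal before sampling, or already found through existing newborn screening (phenylketonuria, screened nationally since 2007) contributes fewer cases than its birth incidence implies.

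Two conclusions are at stake. First, the research hypothesis in the Introduction expects lower frequencies than in countries with consanguineous marriage. Incomplete capture, set against newborn-screening incidence elsewhere, can produce that result with no true difference. Second, a disorder could appear unimportant for a newborn panel because referral does not surface it, or because very few cases were expected at all.

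**Working it through.** **The plan's own figure.** Section 2.2.1 arrives at 1,500 screened children from an assumed frequency of 2%–2.5% and mentions Daniel's formula, n = z²p(1−p)/d², without giving a precision d. The figure therefore cannot be reproduced. Solving for d at n = 1,500 and z = 1.96 gives ±0.71 percentage points at 2% and ±0.79 at 2.5%. The present point does not depend on this.

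**Inputs.**
- Screened children 1,500, frequency 2%–2.5%, annual live births 69,000–73,000 (Section 2.2.1).
- 37 disorders (Section 2.3.5).
- Prevalence below 1:100,000 for most disorders (Discussion).
- Two years of births: 2 × 69,000 = 138,000 to 2 × 73,000 = 146,000, assuming that the earlier rate continues.
- Capture share s, the proportion of affected children who reach the screened group. The article gives none, so the values below are assumptions.

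**Step 1: effect of referral.** Expected cases = births × true incidence × s, so apparent incidence = true incidence × s. With 142,000 births and a true incidence of 1:10,000 there are 14.2 affected births.
- s = 80%: 11.36 cases, apparent incidence 1:12,500.
- s = 10%: 1.42 cases, apparent incidence 1:100,000.

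The eightfold gap comes entirely from referral. Recruiting more children by the same route, with s still differing between disorders, would not remove it.

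**Step 2: chance of finding no case of a rare disorder.** At 1:100,000 there are 1.38–1.46 affected births in two years. With Poisson counts, P(0) = exp(−expected cases):

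| Assumed capture | P(0 cases) |
|---|---|
| 100% | 0.23–0.25 |
| 50% | 0.48–0.50 |
| 10% | 0.86–0.87 |

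**Step 3: chance zeros within the 1,500.** This is sampling variation, separate from referral bias.
- Expected cases: 1,500 × 0.02 = 30 to 1,500 × 0.025 = 37.5.
- Per disorder: 30/37 = 0.81 to 37.5/37 = 1.01.
- If all 37 were equally common, p = 0.020/37 or 0.025/37, and (1−p)^1500 = 0.444 or 0.363.
- Expected number of disorders with no case: 37 × 0.444 = 16.4 or 37 × 0.363 = 13.4.
- Two-sided 95% upper limit for 0 of 1,500: 1 − 0.025^(1/1500) = 0.246%. This is about four times the average per-disorder rate of 0.054%–0.068% (2%/37 to 2.5%/37).

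**Step 4: direction.** Two features can push the ratio up. Children aged up to 18 enter the numerator while only births in 2023–2024 enter the denominator. The Discussion also notes that some disorders begin later and are missed by ENBS; selective screening to age 18 can find these. The sign of the error therefore differs between disorders.

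**The case against.** The panel sentence is a forward-looking remark in the Discussion, not an endpoint or a decision rule. Frequency is one of three factors it names, beside economics and laboratory equipment. A reader might infer that these frequencies will settle the panel, or that disorders with no case will be dropped; the text says neither. The article calls the work a pilot, concedes that ENBS would be needed to assess prevalence thoroughly, and lists the limited number of children as a limitation. This stands, and it limits how strongly the point can be put.

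A reader might also infer that only children already ill can enter. That is not so: similar-disease child deaths in the family are a main criterion, and sibling death, consanguinity and positive family history are additional ones. Newborns in maternity wards are eligible. Nor will all disorders look rare by design, since late-onset ones may be better captured here than by ENBS.

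The 13–16 chance zeros do not measure referral bias, and even full capture of two years' births leaves a 23%–25% chance of no case at 1:100,000. Exact limits are also commonly left to an analysis plan, so their absence is not itself a fault. Finally, Section 3.2 already defines a detection rate per screened child, which is the like-for-like quantity.

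None of this removes the core. After conceding that ENBS is unavailable, the Discussion still matches cases per birth with incidence elsewhere and keeps the panel use, while the spectrum difference it reports is absent from the limitations.

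**Conclusion.** The point holds in a bounded form. As written, the plan compares unlike quantities and lets the result inform a newborn panel, against evidence that it cites itself. Poorly captured disorders will be understated, which can falsely support the hypothesis of lower frequencies; others may be overstated. The size of the referral effect cannot be derived from the article; the eightfold gap rests on assumed capture shares of 80% and 10%. The chance component follows from the plan's own figures plus the simplifying assumption of equally common disorders: about 13–16 of 37 with no case, each zero still compatible with up to 0.25% of screened children. A zero count is therefore uninformative for the panel question.

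**What to change.** - In Task 3 and the Discussion, compare detection rates per screened child, and only with other selective-screening series.
- Do not match any cases-per-birth figure with newborn-screening incidence. Where such a figure is reported (Section 3.4 and the Discussion), label it as an estimate for referred disease subject to incomplete capture.
- Beside the panel sentence, state that a zero or low count is not a ground for leaving a disorder out of the ENBS panel.
- Report exact 95% limits for all 37 disorders, including those with no case. Keep the per-disease ranking, which serves the stated aims, and show it with these limits.
- Add the difference in spectrum between selective and newborn screening to the limitations.

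The cost is a few reworded sentences and one table column, with no new data. The downside is a weaker policy claim and fewer eligible comparators.

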## 5 Ethics and dissemination

This research poses no risk to participating individuals. Study participation does not imply restrictions in any clinical care determined by pediatricians. All study procedures are conducted according to the principles of the Declaration of Helsinki (2013), and patient rights are observed. Participation in the study is voluntary. Informed consent is obtained from all parents and/or legal guardians of children involved in the study. Written informed consent is obtained from the patients’parents and/or legal guardians to publish all subsequent papers under the following conditions: their data must be placed anonymously in the research database without mentioning personal details, i.e., 600 under coded numbers. The study was approved by the Bioethics Committee of the West Kazakhstan Marat Ospanov Medical University (Ref.: No. 7.04, 29/09/2022.)

The dissemination plan includes publishing two articles, not accounting for the Study Protocol. The first paper will report scientific results on set reference values in the group of healthy controls, and the subsequent publication present the research’s final results (in peer-reviewed journals). The dissemination plan does not imply but makes it possible to develop national-scale clinical recommendations to manage IEM in the country.
